## Interventions

### 11a. Interventions for each group

Table 2: Combined Protocol Intervention: Kenya and South Sudan

| **Combined Protocol** |  |
| --- | --- |
| **Admission Criteria** | <125mm MUAC  AND/OR bipedal oedema (+)  AND clinically uncomplicated (i.e. passes appetite test, no Integrated Management of Childhood Illness (IMCI) danger signs/ no serious medical complications) |
| **Treatment Frequency** | <115mm: Weekly  115-<125mm: Bi-weekly |
| **Dosage** | <115mm and/or oedema (+): Two 92g sachets RUTF/day (1000 kcal/day)  115-<125mm : One 92g sachet RUTF/day (500 kcal/day) |
| **Transition from 2 RUTF to 1 RUTF:** | Two consecutive weekly measurements at or above 115mm and no oedema |
| **Cured** | ≥125mm for 2 consecutive measurements and no oedema, with 3 week minimum stay |
| **Default** | Absent for 3 consecutive visits |
| **Non-recovered** | Has not achieved discharge criteria within 16 weeks |
| **Discharge procedures** | Discharge ration of 7 RUTF sachets |
| **Routine medical treatments (as per national protocol):** | For all children with MUAC <115mm and/or bipedal oedema (+) on admission:   - **Amoxicillin:** Give first dose at health facility and then give remainder to caretaker with instructions to give twice daily for 7 days   For all children with MUAC <125mm and/or bipedal oedema (+) on admission:   - **Malaria**: according to national protocol - **Measles:** one vaccine on 4^th^ visit (4^th^ week) (children >6 months) (unless already vaccinated) - **Deworming:** one dose (albendazole or mebendazole) on the second visit (second week) (children >1 year) |
| **Referral Procedures (as per national protocol)** | Any child who develops medical complications and/or is not responding to treatment will be referred for a medical evaluation and/or to the Stabilization Center.  ‘Not responding to treatment’ will be defined in the following way:   - Failure to gain any weight (non-oedematous children) - Failure to start to lose oedema - Oedema still present - Weight loss since admission to program (non-oedematous children) - Failure of appetite test - Weight loss of 5% of body weight - Weight loss for two successive visits |

Table 3- Standard Protocol Intervention- Kenya

| **Standard Protocol- Kenya** | **OTP** | **SFP** |
| --- | --- | --- |
| **Admission Criteria** | - WHZ < -3   And/or   - MUAC < 115mm   And/or   - Bilateral pitting oedema (+/++) | - Discharged from OTP   And/or   - WHZ <-2 to WHZ >-3  and/or - MUAC 115mm < 125mm |
| **Treatment Frequency** | Weekly | 14 days |
| **Dosage** | RUTF 200kcal/kg/day | - Plumpy Sup (500 kcal/day) |
| **Cured** | - MUAC >115mm   And/or  WHZ >-3 Z-score  and   - No oedema for two consecutive visits   and   - Minimum two months stay | Child maintains WHZ >-2 Z-score and/or MUAC ≥125mm for a period of two consecutive weighs/measurements  *For the purposes of analysis, children will be considered ‘cured’ after reaching ≥125mm for a period of two consecutive measurements.* |
| **Default** | Absent for 3 consecutive visits | Absent for 3 consecutive visits |
| **Non-recovered** | Has not achieved discharge criteria within 4 months | Has not achieved discharge criteria within 4 months |
| **Discharge procedures** | - Give a final ration of seven sachets as a weaning off ration - Refer to SFP | N/A |
| **Routine medical treatments** | - **Amoxicillin:** Give first dose at health facility and then give remainder to caretaker with instructions to give twice daily for 7 days - **Malaria**: according to national protocol - **Measles:** one vaccine on 4^th^ visit (4^th^ week) (children >6 months) (unless already vaccinated) - **Deworming:** one dose (albendazole or mebendazole) on the second visit (second week) (children >1 year) | N/A |
| **Referral Procedures** | Any child who develops medical complications and/or is not responding to treatment will be referred for a medical evaluation and/or to the Stabilization Center.  ‘Not responding to treatment’ will be defined in the following way:   - Failure to gain any weight (non-oedematous children) - Failure to start to lose oedema - Oedema still present - Weight loss since admission to program (non-oedematous children) - Failure of appetite test - Weight loss of 5% of body weight - Weight loss for two consecutive visits | |

Table 4- Standard Protocol Intervention- South Sudan

| **Standard Protocol- South Sudan** | **OTP** | **SFP** |
| --- | --- | --- |
| **Admission Criteria** | - WHZ < -3   And/or   - MUAC < 115mm   And/or   - Bilateral pitting oedema (+ /++)   AND   - Appetite test passed - No medical complications - Child clinically well and alert | - Discharged from OTP   And/or   - WHZ <-2 to WHZ >-3 and/or - MUAC 115mm < 125mm   AND   - Appetite test passed - No medical complications - Child clinically well and alert |
| **Treatment Frequency** | Weekly | 14 days |
| **Dosage** | RUTF 200kcal/kg/day | RUSF 500 kcal/day |
| **Cured** | Child maintains MUAC >115mm and/or WHZ >-3 and no oedema for two consecutive visits  Note: The anthropometric indicator (during admission) that is used to confirm SAM should also be used to assess whether a child has reached nutritional recovery (during discharge) | Child maintains WHZ >-2 and/or MUAC >125mm for two consecutive visits  and  6 week minimum stay  *For the purposes of analysis, children will be considered ‘cured’ after reaching ≥125mm for a period of two consecutive measurements.* |
| **Default** | Absent for 2 consecutive visits | Absent for 2 consecutive visits |
| **Non-recovered** | Has not achieved discharge criteria within 2 months | Has not achieved discharge criteria within 3 months |
| **Discharge procedures** | - Give a final ration of seven sachets as a weaning off ration - Refer to SFP | .N/A |
| **Routine medical treatments:** | - **Amoxicillin:** Give first dose at health facility and then give remainder to caretaker with instructions to give twice daily for 7 days - **Malaria**: according to national protocol - **Measles:** one vaccine on 4^th^ visit (4^th^ week) (children >6 months) (unless already vaccinated) - **Deworming:** one dose (albendazole or mebendazole) on the second visit (second week) (children >1 year) | - **Deworming:** one dose (albendazole or mebendazole) on the second visit (second week) (children >1 year) |
| **Referral Procedures** | Any child who develops medical complications and/or is not responding to treatment will be referred for a medical evaluation and/or to the Stabilization Center.  ‘Not responding to treatment’ will be defined in the following way:   - Failure to gain any weight (non-oedematous children) - Failure to start to lose oedema - Oedema still present - Weight loss since admission to program (non-oedematous children) - Failure of appetite test - Weight loss of 5% of body weight - Weight loss for two successive visits | |

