**11c. Strategies to improve adherence to intervention protocols**

Participants will be given a one-on-one counselling session at admission to emphasize the importance of completing treatment, as well as practicing optimal hygiene and infant and young child feeding. Participants will be asked to return used RUTF packets on a weekly basis to monitor adherence and minimize the risk that RUTF packets are sold.

Trained community health workers will follow-up with absent patients to counsel caretakers who may be experiencing difficulties bringing their child to the clinic. Patients who miss 3 consecutive visits will be considered a defaulted participant. Children in both the intervention and control groups will be followed up in the same manner.

All participants in both the intervention and control groups will be referred to the nearest mother-to-mother or father-to-father support groups during and after treatment. The support groups offer health education and social support to caretakers of malnourished and at-risk children.

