### 18b. Plans to promote participant retention and complete follow-up

Participants will be given a careful explanation of the importance of completing treatment and have the opportunity to ask any questions prior to enrolment. As described in section 21, all participants will be given the contact information of two local representatives they can approach if they have any feedback for or wish to express any concerns at any time during the study. A health visitor (a community health worker) will follow-up patients who begin to default from treatment (after one week of missed treatment) to assess the reasons for defaulting and help the family strategize on ways to complete to treatment.

If a family chooses not to bring their child back to complete treatment, the child will be discharged as ‘defaulted’ after 3 weeks of missed treatment. No additional data will be collected on children who default.

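### Table 2 times the measles vaccine by a 4th visit that equals the 4th week only on weekly visits; for children seen bi-weekly from entry it is day 42, after the earliest possible cure on day 28

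*Protocol*

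**What the plan says.** All the governing text is in Protocol section 11a, Table 2 (Combined Protocol).

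- Measles timing: "one vaccine on 4^th^ visit (4^th^ week) (children >6 months) (unless already vaccinated").
- Who receives it: "For all children with MUAC <125mm and/or bipedal oedema (+) on admission".
- Visit frequency: weekly below 115mm, and "115-<125mm: Bi-weekly" for the moderate band.
- Cure: "≥125mm for 2 consecutive measurements and no oedema, with 3 week minimum stay".
- Step-down from two sachets to one: "Two consecutive weekly measurements at or above 115mm and no oedema".

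Table 3 (Kenya, standard protocol) gives the visit frequency for OTP and SFP as "Weekly | 14 days", and Table 4 (South Sudan) sets the same. The measles line in Table 2 is worded as in the OTP columns of Tables 3 and 4. Neither SFP column lists a measles vaccine.

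Other sections speak of weekly contact for everyone. Section 11c says "Participants will be asked to return used RUTF packets on a weekly basis", section 18b counts a child as defaulted "after 3 weeks of missed treatment", and sections 18a and 19 refer to weekly data collection or weekly follow-up visits.

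**The concern.** The measles line treats a visit number and a calendar week as the same thing. That works for children seen weekly. Table 2 applies the line unchanged to children seen every two weeks, for whom the two come apart, and does not say which takes precedence. The table also allows some of those children to be discharged as cured before a 4th visit takes place, and the protocol states no catch-up dose at discharge.

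At stake is delivery of a vaccine that the protocol itself orders for malnourished children. Two facilities following the same table in good faith could vaccinate at different times, or one could discharge a child unvaccinated.

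**Working it through.** **Inputs, all from section 11a.** Visit interval: 7 days below 115mm, and 14 days for 115 to <125mm. The 14-day reading of bi-weekly is supported by the SFP interval for the same MUAC band in Tables 3 and 4. Cure: two consecutive measurements at or above 125mm, no oedema, stay of at least 21 days. Admission is counted as visit 1 and attendance is assumed complete.

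**Formulas.** Day of visit v = (v − 1) × interval. Week = whole part of (day ÷ 7), plus 1.

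**Reproducing the plan's equation of visit 4 with week 4.** Weekly: (4 − 1) × 7 = day 21, and 21 ÷ 7 + 1 = week 4. The two agree. Bi-weekly: (4 − 1) × 14 = day 42, and 42 ÷ 7 + 1 = week 7. They do not.

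| Schedule | Visit days | Visit 4 | Earliest cured discharge |
|---|---|---|---|
| Weekly | 0, 7, 14, 21 | day 21 | day 21, visit 4 |
| Stepped down to bi-weekly on day 14 | 0, 7, 14, 28 | day 28 | day 28, visit 4 |
| Bi-weekly from entry | 0, 14, 28, 42 | day 42 | day 28, visit 3 |

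A child stepped down on day 21 or later still has visit 4 on day 21. On the third schedule, cure on day 28 needs 125mm or more on days 14 and 28; the stay of 28 days exceeds the 21-day minimum.

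**Does the week label settle it?** If week 4 is days 21 to 27, a child bi-weekly from entry has no visit in it (the visits on either side are days 14 and 28). If it means four completed weeks, 4 × 7 = day 28, which is visit 3 and not visit 4.

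**Other ways of counting.** If admission is not counted as a visit, the 4th bi-weekly visit is 4 × 14 = day 56, and the gap widens. If bi-weekly meant twice a week (every 3.5 days), visit 4 would be 3 × 3.5 = day 10.5, which also misses week 4.

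**Gain needed for cure on day 28.** From 124mm: 125 − 124 = 1 mm by day 14 (1 ÷ 14 = 0.07 mm/day). From 120mm: 5 mm by day 14 (5 ÷ 14 = 0.36 mm/day). In both cases 125mm must still be met on day 28. The protocol gives neither the expected MUAC gain nor the proportion already vaccinated, so the number of children affected cannot be computed.

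**Incomplete attendance.** Table 2 tolerates absences short of three consecutive visits, and it states no visit frequency for oedema as such. Take a child admitted with mild oedema and a MUAC just below 125mm, seen weekly, who misses day 7. The attended visits are days 0, 14 and 21, and cure is possible on day 21 at the 3rd attended visit.

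**The case against.** The strongest reply is that the week label is only an approximate gloss and that staff would vaccinate at about four weeks. There is support for this: the South Sudan SFP column in Table 4 times deworming at the second visit and second week although visits are 14 days apart, so the document uses such labels loosely elsewhere. On that reading the dose falls on day 28 and the child cured that day is vaccinated. This stands as a possible reading. It shows that a missed dose is conditional, but it does not remove the conflict, because the line gives both criteria and ranks neither.

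The row is also headed as following the national protocol, and section 11d refers routine care to it. Those national documents may contain a catch-up rule. This cannot be excluded, but the national tables as reproduced give no measles timing for 14-day visits.

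The weekly wording in sections 11c, 18a, 18b and 19 might be taken to imply weekly contact. It conflicts with the explicit frequency row and schedules no day-21 visit.

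A reader might go further and infer that every fast-recovering bi-weekly child is discharged unvaccinated, or that only children bi-weekly from entry can be cured before visit 4. The documents support neither: the first holds only if the visit number governs, and the second only under full attendance. Nor do they support saying that Combined children fare worse than controls here, since neither SFP column orders the vaccine for control children in the same MUAC band.

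**Conclusion.** The point stands as a small internal contradiction in a treatment instruction. Under full attendance and 14-day visits, visit 4 is day 42 for children bi-weekly from entry, three weeks after the day 21 on which visit and week agree. Whether a dose is missed or only its timing varies depends on which half of the line the facility follows. If the visit number governs, an eligible child cured on day 28 misses the dose and the others wait until day 42; if four completed weeks governs, the dose is given on day 28. A weekly child who misses a visit can also be cured before the 4th attended visit.

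Only unvaccinated children over 6 months are concerned, and their number is unknown. The recovery definition, the sample size, the non-inferiority margin and the secondary outcomes are unaffected. The reason to act is that an ordered vaccine can be delivered reliably at negligible cost.

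The deworming line in Table 2 has the same inexact label (the second bi-weekly visit is day 14, in week 3), but no child can be cured before visit 2, so cure cannot pre-empt that dose.

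**What to change.** In the measles line of Table 2, replace the visit-and-week timing with: *one vaccine at the first visit on or after day 21*. Keep the age and prior-vaccination conditions. Tables 3 and 4 can stay as they are.

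With full attendance, weekly children keep day 21 and children stepped down on day 14 keep day 28, both still visit 4. Children bi-weekly from entry get the vaccine on day 28 (visit 3), 42 − 28 = 14 days earlier than under the visit-number reading.

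No extra clause about discharge is needed. Cure requires a stay of at least 21 days, so a cured discharge is always on or after day 21 and the first such visit can never come later than it. This holds with missed visits too.

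The cost is one line of text; the downside is that vaccine must be in stock at that visit.

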## Outcomes

Table 6: Primary and Secondary Outcomes

|  | **Measurement variable** | **Analysis metric** | **Method of aggregation** | **Time point** |
| --- | --- | --- | --- | --- |
| Primary | | | | |
| Recovery | MUAC ≥125mm and no oedema  Note: The definition of recovery in both the control and intervention groups will be defined as two consecutive measurements with a MUAC≥125mm and no oedema. For the purposes of analysis, children receiving the standard protocol will be considered as cured when their MUAC≥125mm and no oedema for two consecutive measurements, even if they continue to receive treatment until they reach a WHZ >-2. | Final value | Proportion | End of treatment |
| Secondary | | | | |
| Coverage | % of children eligible for treatment (MUAC<125mm) who receive it  Note: The coverage surveys will be based on a MUAC-only definition of Global Acute Malnutrition (GAM (MUAC<125mm). Weight and height measurements will not be taken. | Final value | Proportion | Semi-quantitative evaluation of access and coverage (SQUEAC) survey (after final enrolment) |
| Defaulter | Child discharged as defaulter (3 missed visits) | Final value | Proportion | End of treatment |
| Died | Child died during treatment | Final value | Proportion | End of treatment |
| Length of stay | Days in treatment | Duration of time | Sum | End of treatment |
| Average daily weight gain | grams/kilograms/day | Daily | Mean | End of treatment |
| Average daily MUAC gain | mm/day | Daily | Mean | End of treatment |

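### The control SFP cured rule (WHZ and/or MUAC) conflicts with the Table 6 note; read literally, it gives the control arm alone a route to MUAC non-recovery that favours non-inferiority

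*Protocol*

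**What the plan says.** Children enter the study on MUAC below 125 mm and/or mild oedema. There is no WHZ requirement (section 10, Table 1), so a child with low MUAC and WHZ above -2 is eligible.

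- **Control discharge, Kenya SFP (section 11a, Table 3):** "Child maintains WHZ >-2 Z-score and/or MUAC ≥125mm for a period of two consecutive weighs/measurements". The SFP cell gives no minimum stay.
- **Control discharge, South Sudan SFP (Table 4):** "Child maintains WHZ >-2 and/or MUAC >125mm for two consecutive visits", with a six-week minimum stay.
- **Combined Protocol discharge (Table 2):** "≥125mm for 2 consecutive measurements and no oedema, with 3 week minimum stay".
- **Primary outcome (section 12, Table 6):** "The definition of recovery in both the control and intervention groups will be defined as two consecutive measurements with a MUAC≥125mm and no oedema", assessed at end of treatment. Both control SFP cells repeat the MUAC part for analysis: "children will be considered ‘cured’ after reaching ≥125mm for a period of two consecutive measurements".
- **Table 6 note on timing:** a control child who meets the MUAC definition is counted as cured "even if they continue to receive treatment until they reach a WHZ >-2".
- **Same-indicator note (Table 4, South Sudan OTP cell only):** the admission indicator "used to confirm SAM should also be used to assess whether a child has reached nutritional recovery (during discharge". Neither SFP cell says this, and the Kenya table does not say it at all.

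**The concern.** The tables disagree on how a control child leaves treatment. Under an either-index rule, a child at MUAC ≥125 mm on two measurements has already met the discharge rule and would not be held until WHZ exceeds -2. The Table 6 note assumes that such a child may be held.

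The disagreement bears on the primary outcome. On the literal reading of *and/or*, a child admitted on low MUAC whose WHZ is above -2 can be discharged as cured while MUAC is still below 125 mm. Section 18a lists data collection at admission, at weekly visits and at discharge, so no later MUAC is planned. The child's programme exit is cured, but the primary outcome is not recovered. In the Combined arm, cured discharge and the outcome use the same MUAC criterion, so this route to non-recovery exists only in control. The Table 6 note covers only the opposite order, with MUAC reached first and WHZ later.

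In a non-inferiority trial, anything that lowers observed control recovery alone makes the claim easier to reach.

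**Working it through.** **Inputs from section 14 and Table 7:** recovery 85% in both arms, margin 10 points, 12 clusters per arm, 100 children per cluster, ICC 0.05, two-sided 5% (one-sided 2.5%), power 80%.

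**Assumed input:** f, the points of control recovery lost because children leave on WHZ with MUAC below 125 mm although they would have reached 125 mm had they been followed to that criterion. The documents give no figure for f. The range shown is 0 to 10 points.

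**Step 1: reproduce the plan's sample size.**
- Per arm without clustering: 2 × 0.85 × 0.15 × (1.96 + 0.84)² / 0.10² = 200.1, rounded up to 201.
- Design effect: 1 + (100 − 1) × 0.05 = 5.95.
- 201 × 5.95 = 1196 per arm, or 11.96 clusters of 100, rounded up to 12. This agrees with the plan.
- Power with 12 × 100 per arm: SE = √(2 × 0.85 × 0.15 × 5.95 / 1200) = 0.0356, and Φ(0.10/0.0356 − 1.96) = 80.3%.

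**Step 2: effect of f at the edge of the margin.** Take rates of 85% control and 75% intervention, with every child followed to the MUAC criterion. Observed control recovery is 0.85 − f, so the observed difference is 0.10 − f.

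P(declare non-inferiority) = Φ(f / SE − 1.96), where SE = √{[(0.85 − f)(0.15 + f) + 0.75 × 0.25] × 5.95 / 1200}.

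Example at f = 0.05: SE = √[(0.1600 + 0.1875) × 5.95 / 1200] = 0.0415, and Φ(0.05/0.0415 − 1.96) = 22.5%.

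| Points lost (f) | Effective margin | P(declare non-inferiority) |
|---|---|---|
| 0 | 10 | 2.5% |
| 1 | 11 | 4.4% |
| 2 | 12 | 7.2% |
| 3 | 13 | 11.1% |
| 5 | 15 | 22.5% |
| 10 | 20 | 64.0% |

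**Step 3: exits and points lost are not the same.** Some early leavers would never have reached 125 mm. If 5% of control children left this way and 85% of them would have reached it (both assumed), f = 0.05 × 0.85 = 4.25 points and the probability is 17.6%. If it happened only in Kenya, which has half the clusters, a 5-point loss there is 2.5 points overall and the probability is about 9%.

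**Step 4: f under each reading of *and/or*.**
- Either index suffices: f can exceed 0.
- Both indices are needed: a child with MUAC below 125 mm cannot leave as cured, so f = 0.
- The admission indicator governs: a child admitted on MUAC cannot leave as cured on WHZ alone, so f = 0 for these children.

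The SFP cells do not say which reading applies.

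**The case against.** **The literal reading may not be how the rule works.** The Table 6 note fits a rule that needs both indices. The South Sudan OTP note shows the admission indicator governing a similarly worded rule. A MUAC of 115 to below 125 mm is also an SFP admission criterion, so an either-index rule could discharge a child who still qualifies for admission. This stands as a reason not to treat the exits as established. It does not remove the conflict, because no SFP cell states either alternative.

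**The classification is not missing.** One MUAC definition applies to both arms, and by it the WHZ-only leaver is not recovered. That is right. What is unsettled is whether and how often such children arise, and nothing separates them from children who did not respond.

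**The trial compares whole protocols, discharge rules included.** On an end-of-treatment outcome, a child who leaves below 125 mm is a real non-recovery. With 5 points lost, the control rate on the stated outcome is 80%, which is 5 points above 75% and inside the margin. Declaring non-inferiority would then not be an error on that outcome. This stands: the probabilities in the table are error rates only relative to the rate had these children been followed to the MUAC criterion.

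**A reader might infer that the whole trial is biased toward non-inferiority.** The document does not support that. In the Kenya table, OTP and SFP each carry the limit "Has not achieved discharge criteria within 4 months", against 16 weeks in the Combined arm. The extra time can raise control recovery. South Sudan control children default after two missed visits, against three in the Combined arm, which can lower it. The net direction is not known.

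**Sensitivity analyses usually sit in the SAP, which is not at hand.** Accepted. The point rests on the contradiction between the tables, not on the absence of an analysis.

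**Conclusion.** The point holds in a conditional form. Tables 3 and 4 contradict the Table 6 note on how control children leave treatment. On the literal reading, the control arm alone has a cured exit that the primary outcome scores as non-recovery. If such exits occur, this route favours non-inferiority by one point of margin for each point of control recovery lost. At 85% v 75%, the chance of declaring non-inferiority rises from 2.5% to about 4% at 1 point, 7% at 2 and 22.5% at 5. The figures use the section 14 design, a normal approximation and an assumed f. Zero is a possible value, and it is the result if both indices are needed or the admission indicator governs. Neither the occurrence of these exits nor a net bias of the trial is established.

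**What to change.** 1. Reconcile the SFP cured cells of Tables 3 and 4 with the Table 6 note, stating what *and/or* means for children admitted on MUAC. Which discharge rule applies is for the sponsor and the national protocols; none is proposed here.
2. Keep the MUAC definition as the primary outcome in both arms.
3. Extend the Table 6 note to the mirror case. Record control children who exit on WHZ with MUAC below 125 mm as a separate category, with MUAC and WHZ at exit, and report the number by country.
4. Prespecify, in the protocol or in the SAP if it is not already there, a sensitivity analysis of the non-inferiority comparison with these children counted as recovered. This over-credits control to the extent that some would not have reached 125 mm. Together with the primary analysis it therefore brackets the control rate had they been followed. State in advance that the conclusion is not robust if the two analyses disagree.

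The cost is some wording, one exit code and one more analysis. Section 15 already has weight, height and MUAC taken at the facilities. The downside is that a non-inferiority claim may be slightly harder to defend. If such exits are rare, the two analyses should agree and little is lost.

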### 6b. Explanation for choice of comparators

The Combined Protocol will be compared against the Standard Protocol (the national protocol in each country). The standard protocol includes treatment of SAM in an outpatient therapeutic program using RUTF (200 kcal/kg/day) and MAM in a supplementary feeding program using RUSF (500 kcal/day), as approved by WHO, UNICEF, WFP, and the Ministries of Health in each country. Both the Combined Protocol and the Standard Protocols for each country are described in detail in section 11.

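### South Sudan control children are exited as defaulters after 2 missed visits, against the 3-visit rule that defines the outcome and governs the Combined arm

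*Protocol*

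**What the plan says.** The protocol states a default rule in six places.

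- Section 11a, Table 2 (Combined Protocol, both countries): "Absent for 3 consecutive visits".
- Section 11a, Table 3 (Standard Protocol, Kenya), OTP and SFP: the same 3 visits.
- Section 11a, Table 4 (Standard Protocol, South Sudan), OTP and SFP: "Absent for 2 consecutive visits".
- Section 11c, for patients in general: "Patients who miss 3 consecutive visits will be considered a defaulted participant". It adds: "Children in both the intervention and control groups will be followed up in the same manner".
- Section 12, Table 6, the Defaulter outcome: "Child discharged as defaulter (3 missed visits"), with no exception by arm or country.
- Section 18b: "the child will be discharged as ‘defaulted’ after 3 weeks of missed treatment". The same paragraph says that nothing further is recorded on a child who has defaulted.

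Section 6b makes the national programme the comparator: "The Combined Protocol will be compared against the Standard Protocol (the national protocol in each country"). For recovery, Table 6 overrides the national discharge rule: "For the purposes of analysis, children receiving the standard protocol will be considered as cured when their MUAC≥125mm". The Defaulter row has no such override.

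**The concern.** Default is a prespecified secondary outcome. In South Sudan the two randomised arms leave treatment under different default rules, so part of any difference in default could come from the definition and not from the treatment.

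The outcome definition does say 3 missed visits, but what it counts is a discharge made by the facility. In South Sudan control, Table 4 triggers that discharge at 2. Staff who follow Table 4 are doing what section 6b asks of a national-protocol comparator. Once the child has been exited, section 18b ends recording, so whether the child would have come back before a third missed visit may never be known. An analysis plan cannot recover data that the protocol says not to collect.

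The error would favour the Combined Protocol on default.

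**Working it through.** **Rules within each country**

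| Country | Control | Combined | Same rule? |
|---|---|---|---|
| Kenya | 3 visits (Table 3) | 3 visits (Table 2) | Yes |
| South Sudan | 2 visits (Table 4) | 3 visits (Table 2) | No |

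Section 8 gives 6 control clusters per country, so the mismatch affects 6 of 12 control clusters.

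**Absence needed to become a defaulter**

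Days from the last attended visit to the k-th consecutive missed visit = k × visit interval. Intervals come from section 11a: weekly in OTP and for Combined children below 115 mm; every 14 days in SFP and for Combined children from 115 to below 125 mm.

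| Schedule | 2 visits | 3 visits |
|---|---|---|
| Weekly | 2 × 7 = 14 days | 3 × 7 = 21 days |
| 14-day | 2 × 14 = 28 days | 3 × 14 = 42 days |

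South Sudan control children are thus exited 7 days earlier on the weekly schedule and 14 days earlier on the 14-day schedule.

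**Section 18b**

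Three weeks is 21 days, which equals 3 visits on the weekly schedule only. On the 14-day schedule, 21 days from the last attended visit takes in one missed visit (day 14). Counted from the first missed visit it ends on day 14 + 21 = 35 and takes in two (days 14 and 28). Neither count reaches the third missed visit on day 42. This discrepancy applies equally to both arms.

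**Possible size, for illustration only**

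Let d be the true 3-visit default risk, equal in both arms. Let s be the share of South Sudan control children who miss exactly two consecutive visits, would return, and would not later default under the 3-visit rule. The last condition keeps s from overlapping with d. The protocol gives neither value; both are assumed. Table 4 is assumed to be followed, and clusters are taken as equal in size.

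- Apparent South Sudan control default = d + s. Apparent risk ratio = d / (d + s).
- Apparent pooled control default = d + s/2, since 6 of 12 control clusters are affected. Apparent risk ratio = d / (d + s/2).

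| d | s | Risk ratio, South Sudan | Risk ratio, pooled |
|---|---|---|---|
| 0.10 | 0.02 | 0.10/0.12 = 0.83 | 0.10/0.11 = 0.91 |
| 0.10 | 0.05 | 0.10/0.15 = 0.67 | 0.10/0.125 = 0.80 |
| 0.05 | 0.05 | 0.05/0.10 = 0.50 | 0.05/0.075 = 0.67 |
| 0.15 | 0.05 | 0.15/0.20 = 0.75 | 0.15/0.175 = 0.86 |

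The true ratio is 1.00 in every row. Each percentage point of s adds 1 point to South Sudan control default and 0.5 point to pooled control default.

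**The case against.** The strongest reply is that the outcome is already defined. Table 6 sits in the Outcomes section, says 3 missed visits and makes no exception, and section 11c says the same for all patients. Table 4 describes national programme practice. On this view the analysis follows Table 6, and deriving default from visit dates is a matter for the statistical analysis plan, which is not at hand.

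Much of this stands. A reader who compares the tables might infer that the protocol never says which default rule governs the outcome. That goes too far: Table 6 and section 11c both state 3 visits. What remains is that the stated outcome depends on a discharge set at 2 in one arm of one country, and that recording may end there. An analysis plan can derive 3-visit status only if the visits after the exit are recorded.

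A reader might also infer that the early exit lowers control recovery and so eases a non-inferiority conclusion on the primary outcome. The protocol does not support that. It does not say how defaulters enter the recovery denominator. If they count as not recovered, control recovery would fall. If they are left out, it could move either way.

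Two further points are fair. Section 18b has a community health worker follow up after one missed week, which may keep s small. And the missing analysis note is only supporting evidence, because cure needed one for a different reason: the national cure criteria also admit weight-for-height.

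**Conclusion.** The conflict between Table 4 and the rule in Table 6, section 11c and Table 2 is certain from the text. If Table 4 is followed and recording ends at exit, control default is raised in 6 of 12 control clusters by definition alone, in favour of the Combined Protocol. Kenya has no difference between arms.

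The size is unknown. The risk ratios of 0.50 to 0.91 follow from assumed inputs and show only what modest returner shares could do. The effect on recovery is undetermined in direction and size. The 3-week wording in section 18b is a separate inconsistency that does not differ by arm.

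This should be fixed. It concerns a secondary outcome in one arm of one country, but it is cheap to correct before data are lost and hard to repair afterwards.

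**What to change.** 1. Add a note to the Defaulter row of Table 6: for analysis, default in all arms and both countries is 3 consecutive missed scheduled visits, derived from visit dates, whatever the facility's own exit rule.
2. Keep South Sudan control children under study recording until the third missed visit, even if the facility has exited them at the second. A child who returns before then keeps the same study ID and continues to be recorded.
3. Replace the 3 weeks in section 18b with the same 3-visit rule, and make clear that recording stops only once that rule is met.
4. If records after the exit are missing, apply the 2-visit rule to both South Sudan arms from recorded visits, as a within-country sensitivity analysis only. Used as the main definition it would leave the pooled outcome with 2 visits in one country and 3 in the other, against Table 6.

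The cost is a table note, a derived variable, changed wording in section 18b, and an amendment to the three ethics committees under section 23. The six South Sudan control sites record a few returning children more, and section 19 already places a full-time research officer at each. The sensitivity analysis needs no new data. Trial default rates will differ from routine programme reports in South Sudan, which should be said when results are reported.
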